### Stakeholder interviews

Attempts will be made to replace staff who withdraw from the stakeholder interview.

### Intervention

At discharge, eligible patients will be provided with a swab kit containing two culture swabs, two ampoules of saline, three alcohol-free hand wipes, a packet of gauze, a return envelope and rigid packaging, two labels, a pen and a set of instructions. At a prearranged appointment time convenient to the participant and researcher, and within 1–21 days postdischarge, patients will perform self-swabbing assessed remotely by a researcher (via Microsoft (MS) Teams). The researcher will undertake all MS Teams meetings in a private setting with a locked door to maintain participant privacy and confidentiality. After checking, the wound edges remain closed and non-infected so that the patient still meets the study eligibility criteria. The researcher will use a checklist to record whether the participant is able to comply unaided with each step of the instructions, while maintaining the sterility of the swab. The researcher will also ensure infection prevention procedures are followed and provide guidance if needed. A distress protocol will be available, as required.

The researcher will arrange for completed swabs to be collected as soon as possible after swabbing and couriered to an independent UK laboratory (based in Basildon), used by the NHS. In the 2 weeks following the observed swabbing, participants will take part in a semistructured online interview exploring acceptability and usability of self-swabbing, the kit and the instructions. Interviews, conducted by the researcher or delegated member of the research team, will be audio-recorded, transcribed verbatim, pseudo-anonymised and analysed using thematic analysis.^23^

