**Methods and analysis:**

TREASURE is a multicentre, mixed-methods feasibility study. A total of 40 patient participants and 10 staff stakeholders will be included. 40 adult patients undergoing cardiac surgery via median sternotomy will be recruited from Harefield Hospital (n=25) and the Royal Sussex County Hospital (n=15). Eligible participants will receive a coproduced self-swabbing set of instructions and kit at discharge and perform wound swabbing at home within 1–21 days, observed remotely by a researcher via Microsoft Teams. Swabs will be couriered to a central laboratory for bacterial culture with antimicrobial susceptibility testing for pathogens.

The primary feasibility outcome is the proportion of patients successfully completing self-swabbing at home to obtain usable culture swabs with samples received at the laboratory within 24 hours and deemed suitable for processing. Secondary safety and acceptability outcomes include usability of the kit and instructions; patient satisfaction; viability of samples for laboratory analysis; and recruitment and retention rates. A 30-day follow-up will capture wound complications, antibiotic prescribing and healthcare utilisation via patient questionnaires, case note review, general practitioner confirmation and patient interviews. 10 staff stakeholders will be interviewed to inform pathway development.

Quantitative data will be analysed descriptively, with proportions reported alongside 95% CIs. Qualitative data from patients will undergo thematic analysis, and stakeholder interviews will be coded using Normalisation Process Theory. An early health economic model will be developed to explore resource use, costs and proportions of appropriate and timely antibiotic use between current pathways and a proposed pathway, including self-swabbing.

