### Withdrawal criteria

Participation in this study is voluntary. Patients are not required to participate and may decide to withdraw at any time. Participants may be discontinued from study participation on request, through non-compliance, through loss to follow-up, or if they are deemed ineligible after consent has been obtained.

Participants who no longer wish to participate can contact the researcher using the contact details provided in the PIS. Any data submitted prior to withdrawal will still be used in the study. Patients will no longer receive any contact from the research study, although they will continue to receive standard surgical care follow-up.

Study data already recorded in patient records for non-responding participants will be kept unless they explicitly withdraw their consent. Discontinued participants will be assessed for adverse events (AEs) at the final study-required contact (days 28–30) with continuing assessment of procedure-related AEs until these are resolved or stable (ie, unlikely to resolve or managed successfully with treatment). Attempts will be made to replace participants who withdraw post consent, are lost to follow-up or do not meet final eligibility criteria.

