## Outcomes

### Primary outcomes

Feasibility of home-based wound self-swabbing, defined as the proportion of patients completing the procedure successfully (ie, compliance with swabbing instructions) with samples received at the laboratory within 24 hours, and deemed suitable for processing.

Safety of the process, assessed through adherence to swabbing protocol, AEs and participant-reported concerns.

Acceptability of the swabbing process, assessed through Likert scale ratings and qualitative interviews.

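### The acceptability interview follows the observed swab and may be held by its supervisor, with no described route for kit recipients who choose not to swab, so acceptability may be biased upward

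*Protocol article*

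**What the plan says.** - **Status of the outcome.** Primary outcomes lists "Acceptability of the swabbing process, assessed through Likert scale ratings and qualitative interviews". The abstract says "Secondary safety and acceptability outcomes include usability of the kit and instructions; patient satisfaction", which places acceptability among the secondary outcomes.
- **Timing.** Under Intervention: "In the 2 weeks following the observed swabbing, participants will take part in a semistructured online interview exploring acceptability". The kit is handed over at discharge, and the swab is taken 1 to 21 days later.
- **Who interviews.** "Interviews, conducted by the researcher or delegated member of the research team, will be audio-recorded".
- **Who supervises the swab.** "patients will perform self-swabbing assessed remotely by a researcher", using a checklist of the steps done unaided. In addition, "The researcher will also ensure infection prevention procedures are followed and provide guidance if needed".
- **Those who leave.** Under Withdrawal criteria, patients who withdraw are not contacted again by the study. Discontinued participants have an adverse-event assessment at days 28–30, and no acceptability item is mentioned. "Attempts will be made to replace participants who withdraw post consent, are lost to follow-up or do not meet final eligibility criteria".
- **Other sources on reluctance.** Reasons for declining, where offered, go into the screening data (Ethics and dissemination). Barriers to participation fall under the secondary outcome on recruitment and retention.

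**The concern.** Two separate mechanisms could make acceptability look better than it is.

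The first is selection. The interview is timed from the observed swab, so a patient who takes the kit and decides against using it has no described occasion to say so. Up to 21 days pass between receiving the kit and swabbing, which leaves time for reluctant patients to fall away. The study's own survey work (Patient and public involvement) shows that reluctance exists: 75% of respondents in the first survey were supportive, and the second recorded fears of disturbing healing, contaminating the wound or swabbing incorrectly. Patients who hold those fears strongly are plausibly the ones who will not swab.

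The second is courtesy. A participant may be asked to judge the process by the person who watched, coached and scored them.

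At stake is whether the study can say that patients given a kit find self-swabbing acceptable, or only that patients who went through with it did. Who is approached and who asks the questions cannot be repaired at analysis.

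**Working it through.** **The plan's own figure.** The only precision figure concerns swabbing success: 90% of 40, that is 36/40, with an exact 95% CI of 76% to 97%. The Clopper-Pearson interval for 36/40 is 76.3% to 97.2%, so the figure reproduces. It says nothing about acceptability and does not change here.

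**What the text fixes.** Three provisions read together give the selection path:
1. The interview is timed from the observed swab.
2. Withdrawal ends study contact, and the later check on discontinued participants is for adverse events.
3. Replacement is attempted for those who withdraw, are lost or prove ineligible.

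A patient who declines to swab and withdraws or is lost can thus be replaced by one who swabs, with no acceptability data from the first.

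**Illustration of selection (assumed inputs).** The documents give no non-swabbing rate and no acceptability rate. Suppose 40 participants swab and 36 find it acceptable. Suppose *m* further eligible consenters did not swab and were replaced, and a share *q* of them would have found it acceptable. The rate among all eligible consenters is (36 + *m·q*) / (40 + *m*).

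| *m* | *q* = 0 | *q* = 0.5 | *q* = 0.9 |
|---|---|---|---|
| 2 | 36/42 = 85.7% | 37/42 = 88.1% | 90% |
| 4 | 36/44 = 81.8% | 38/44 = 86.4% | 90% |
| 8 | 36/48 = 75.0% | 40/48 = 83.3% | 90% |
| 12 | 36/52 = 69.2% | 42/52 = 80.8% | 90% |

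The last column matters: if non-swabbers feel as swabbers do, there is no bias.

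**Illustration of courtesy answers (assumed inputs).** Let true acceptability be *p* and let a share *d* of the dissatisfied answer favourably. The observed rate is *p* + (1 − *p*)·*d*. With *p* = 0.80:
- *d* = 0.10: 0.80 + 0.20 × 0.10 = 82%
- *d* = 0.25: 0.80 + 0.20 × 0.25 = 85%
- *d* = 0.50: 0.80 + 0.20 × 0.50 = 90%

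These tables show the direction and sensitivity of a possible bias. They are not estimates for this study.

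**The case against.** The case on the other side is substantial, and much of it narrows the point.

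- **Likert ratings.** A reader might infer that the ratings, too, are taken only after the swab and by its supervisor. The documents do not support that. The sentence on timing concerns the interview, and the article does not say when, how or by whom the ratings are collected. Such detail may sit in the full protocol.
- **Who is replaced.** A reader might infer that everyone who fails or stops at the call is replaced and unheard. Non-compliance is a ground for discontinuation but is not named in the replacement sentence, and nothing confines the interview to those who succeeded.
- **Wound status.** Participants found ineligible at the call because of their wound have not rejected swabbing. Their absence need not bias acceptability.
- **Barriers.** A reader might infer that non-swabbing would be hidden. It would not: retention, adherence, barriers to participation, missing-data counts and a participant flow diagram are all planned. They would show how many did not swab, but they are not acceptability data from those patients.
- **Experience.** Someone who never swabbed can give only anticipated acceptability. Pooling that with experienced acceptability over a single denominator mixes two constructs, so a pooled figure should not be the main result.
- **Decision.** The only progression criterion stated concerns swabbing success. No acceptability threshold exists, so no stated decision turns on this.

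What survives is that no acceptability route is described for eligible consenters who choose not to swab, and that supervisor and interviewer may be the same person.

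**Conclusion.** The point holds as a risk of upward bias in the acceptability interview, through selection and through the possible overlap of supervisor and interviewer. It would be too strong to say that the design does push acceptability upward. The direction is likely, but the effect is not demonstrated, and its size cannot be derived from the documents. It depends on how many eligible kit recipients do not swab, how their views differ, and how far participants soften answers to the person who supervised them. Under the assumptions shown, selection could take 90% down to anywhere between 69% and 88%, or leave it unchanged.

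The status of acceptability, primary in the outcomes section and secondary in the abstract, must also be reconciled. The concern stands under either label. The change is worth making before recruitment because it is cheap and cannot be made afterwards.

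**What to change.** 1. Amend the Intervention section so that every eligible kit recipient who does not swab, or who stops at the call, and has not withdrawn from contact, is offered a short acceptability interview and the Likert items. At the point of withdrawal, invite an optional rating and reason.
2. Report these responses separately, beside the swabbers' result, with the number of eligible kit recipients, the number who swabbed and the number who responded. Do not count participants made ineligible by wound status as non-acceptors.
3. Where possible, have the delegated team member whom the article already permits conduct the interview, not the person who supervised that swab.
4. Have the Likert items self-completed, and state when they are collected.
5. Make the abstract and the outcomes section agree on whether acceptability is primary or secondary.

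Cost: a minor amendment, a few extra short contacts, one self-completed form and slightly harder interview scheduling. Some non-swabbers will not respond. Sample size and clinical care are unaffected.

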### Follow-up and data collection

Follow-up data will be collected at 30 days postoperation. Patients’ wounds will be assessed for infection or complication using the UKHSA wound monitoring questionnaire (and image review) via digital monitoring. The researcher will telephone the patient to collect any readmission, treatment or use of NHS resources data. The GPs of patients prescribed antibiotics will be contacted to obtain prescribing details. Medical case note review will be undertaken to identify those with confirmed evidence of wound infection and the management strategy and antibiotics used. The time taken to transport swabs to the laboratory will be documented as well as the condition of the wound swabs on arrival (usability). Samples will be processed for culture and antimicrobial susceptibility testing to confirm their viability. The results of these study swabs will not be shared with participants or the surgical team routinely. Data will be stored using Research Electronic Data Capture (REDCap), with full audit trails. AEs reviews will take place at any time point throughout the study duration.

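### The swab is timed from discharge but the only scheduled wound assessment from surgery, so late swabbers get little or no structured wound follow-up after swabbing

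*Protocol article*

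**What the plan says.** The Intervention section counts the swab from discharge: "within 1–21 days postdischarge, patients will perform self-swabbing assessed remotely by a researcher". It then places an interview after the swab: "In the 2 weeks following the observed swabbing, participants will take part in a semistructured online interview". The stated subject of that interview is how acceptable and usable the process, kit and instructions are.

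Follow-up and data collection uses a different origin: "Follow-up data will be collected at 30 days postoperation". Under that heading patients' "wounds will be assessed for infection or complication using the UKHSA wound monitoring questionnaire (and image review) via digital monitoring", and a telephone call collects readmissions, treatment and NHS resource use. The same section lets adverse events be reviewed at any point while the study runs, without scheduling a review in relation to the swab.

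Two other places give a similar number with no origin. The abstract says "A 30-day follow-up will capture wound complications, antibiotic prescribing and healthcare utilisation". Withdrawal criteria says "Discontinued participants will be assessed for adverse events (AEs) at the final study-required contact (days 28–30", closing bracket omitted here.

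Primary outcomes includes "Safety of the process, assessed through adherence to swabbing protocol, AEs and participant-reported concerns". The section on data protection and management explains that only closed, uninfected-looking wounds are included, in order to limit the chance that patients carry infection into the wound.

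**The concern.** Harm from swabbing can appear only after the swab. To describe it, each participant needs a known and preferably equal period of observation that starts at the swab. Here the exposure follows one clock and the structured wound assessment another, and the gap between the clocks is the length of stay, which the eligibility criteria do not limit. Elective and urgent patients are both admitted.

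The study has no comparator, so the order of swab and event is one of the main ways to judge whether an event could be related to swabbing. If some participants are assessed about three weeks after the swab and others within a day or two, or beforehand, a low count of wound problems could partly reflect short observation. Analysis cannot repair this afterwards, because wound status that was never assessed cannot be recovered.

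**Working it through.** **The plan's own figure.** The article gives no figure for time observed after the swab. Its one reproducible statistical figure is the exact 95% interval for 90% success in 40 patients: 36/40 gives 76.3% to 97.2%, matching the stated 76% to 97%. This point does not affect it.

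**Inputs.**
- Swab day after discharge, d = 1 to 21 (Intervention).
- Structured assessment on postoperative day 30 (Follow-up and data collection).
- Interview up to 14 days after the swab (Intervention).
- Days from operation to discharge, L: not given, so a range is assumed.

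**Formulas.** The swab falls on postoperative day L + d. Time from swab to structured assessment is 30 − (L + d).
- Earliest swab (d = 1): 29 − L days.
- Latest swab (d = 21): 9 − L days.
- Difference at the same stay: (29 − L) − (9 − L) = 20 days, whatever L is.
- The assessment precedes the latest swab when 9 − L < 0, that is, for L of 10 days or more.

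**Results by assumed stay.** The last two columns are shares of the 21 permitted swab days. They are shares of patients only if swab days are spread evenly, which is a further assumption.

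| L (assumed) | Swab day 1: days to assessment | Swab day 21: days to assessment | Swab days leaving under 7 days | Swab days after day 30 |
|---|---|---|---|---|
| 5 | 24 | 4 | 3/21 = 14% | 0 |
| 7 | 22 | 2 | 5/21 = 24% | 0 |
| 9 | 20 | 0 | 7/21 = 33% | 0 |
| 10 | 19 | −1 | 8/21 = 38% | 1/21 = 5% |
| 14 | 15 | −5 | 12/21 = 57% | 5/21 = 24% |

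A negative value means that the assessment comes before the swab; such days are also counted in the under-7 column.

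**Order of the interview and the final contact.** The interview can fall as late as 21 + 14 = 35 days after discharge, or postoperative day L + 35 (day 42 for L = 7). Take the three possible origins of days 28–30 in Withdrawal criteria:
- From operation: the contact precedes the latest interview, and a day-28 contact precedes a day-21 swab once 28 − (L + 21) < 0, that is, from L = 8.
- From discharge: day 28 is 28 − 21 = 7 days after the latest swab, but still before the latest interview on day 35.
- From the swab: the contact follows both the swab and the interview.

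The text does not say which applies.

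**The case against.** The strongest reply is that the day-30 assessment is not the safety outcome. Primary outcomes defines safety by adherence, adverse events and participants' concerns, and does not name the wound questionnaire. Adherence is watched live. Adverse events may be reviewed at any time, the interview brings every participant into contact within two weeks after the swab, and case notes and GP records may reveal treated infections. A reader might infer from the two clocks that late swabbers go almost unobserved. The documents do not support that: it is the scheduled wound assessment and resource-use call that may be short or missing, not all contact. What does not stand is the idea that these routes replace a scheduled assessment. The any-time review has no date, the interview has another subject, and case-note and GP review are described under the same 30-day follow-up.

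A reader might also infer that infections arising before the swab would be counted against swabbing. The researcher checks at the video appointment that the wound is closed and not infected, which largely prevents this among those who swab. Problems resolved before the swab, and earlier treatment or service use, can still enter the 30-day record.

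A third tempting inference is that the final adverse-event contact precedes the swab. That requires days 28–30 to run from the operation, which is not stated, and the sentence concerns discontinued participants, whose procedure-related events are in any case followed until resolved or stable.

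Finally, the study is small and descriptive, its stated progression criterion is the 90% swabbing success rate, and no comparison of event rates is planned. The abstract also places safety among the secondary outcomes, unlike the outcomes section. The full protocol, to which safety reporting is referred, may define event windows. These points lower the weight of the concern. They do not remove the mismatch, which is in the stated text.

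**Conclusion.** The mismatch is explicit, and its core needs no assumption about stay: a day-21 swab leaves 9 − L days to the only scheduled structured wound assessment, and participants with equal stays can differ by 20 days. The reversed order needs a stay of at least 10 days together with a late swab. The documents allow this but give no length of stay, so its frequency is unknown, and the percentages above are illustrations that also assume evenly spread swab days.

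The supportable conclusion is that infection introduced by swabbing is not systematically captured in late swabbers. It does not follow that such infections would be missed altogether, or that the feasibility estimate is affected. This should be fixed because safety is listed as a primary outcome and the remedy is cheap. It does not threaten the study's stated progression criterion.

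**What to change.** 1. Tie one remote contact, covering adverse events and the wound questionnaire, to the swab date at a fixed interval that is the same for all who swab. The sponsor should choose the interval. The contact could accompany the post-swab interview if that is held at a set time rather than anywhere within its two weeks.
2. Report events with onset after the swab separately from earlier ones.
3. Keep the day-30 postoperative record for surveillance and economic data.
4. Give one stated origin for the abstract's 30-day follow-up, the days 28–30 contact in Withdrawal criteria and the day-30 collection in Follow-up and data collection. Make all three consistent with the swab and interview windows, so that a contact called final is the last one.

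The cost is a protocol amendment and one short remote contact rescheduled or added. Recruitment is planned for January to February and the study runs to May 2026. Even a participant discharged on 31 March, a month after recruitment is due to close, would swab by 21 April, so a contact after the swab should fit.

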#### Staff stakeholder interviews

Ten stakeholders will be interviewed. Stakeholders are people who contribute to or influence the usual care surgical wound follow-up pathway and will be identified through stakeholder mapping. Stakeholders from the two participating sites will likely include surveillance staff, infection and wound care nurses, microbiologists and surgeons. In addition, other stakeholders, including GPs, laboratory staff and representatives from companies that make self-testing kits and commissioners will also be approached. The usual care team and the research team will use convenience sampling to invite individuals for interview that represent stakeholder professional groups. The focus of the interviews is to explore how self-swabbing at home can fit into the existing pathway. Stakeholder interviews will be conducted online by the researcher, audio-recorded, transcribed verbatim, pseudo-anonymised and analysed using Normalisation Process Theory.^24^

